### Collection and management of specimens

The blood samples of the patients will be collected at their first visit, transported by cold chain and stored in the Biological Specimen Bank (BSB) at Xuanwu Hospital. Every specimen has a form attached to record the information pertaining to collecting, transporting, storing and using the specimens. The form is transported and stored together with the specimen. The remaining specimens will be destroyed in the BSB at Xuanwu Hospital when the CIAP has been completed.

Some specimens and DICOM data will be transported to Tiantan Hospital to be tested and analyzed when CIAP-2 is being carried out.

### Measures to reduce bias

*Control of selection bias* This is a nationwide population-based study. Twenty centers selected from different regions of China are involved in this study. The status of diagnosis and treatment in different regions of China will be investigated in this study and will be involved in the final analysis. In addition, the patients in each center will be screened consecutively according to the selection criteria.

*Control of information bias* Blinding is being adopted in this study. The clinical research associates (CRAs) will be blinded to the study design. The statistical analysis will also be conducted blindly.

A standardized training program will be created and implemented to ensure that all of the work is undertaken by well-trained CRAs and CRCs.

The double-check process will be implemented in the process of data collection. The quality of the data will be evaluated again before analysis. Unqualified data will be corrected if possible or will be removed if the information about its accuracy is not available. The impact of missing information will be fully considered and will be subject to special analysis.

Regularly communicating with the patients will help improve the quality of the follow-up. The CRAs will call the patients on a regular basis. Furthermore, mobile applications, such as Wechat (an instant messaging and social media application), will be used to establish effective communication channels. In the case of a nonresponding patient, the CRA will try to contact the patient again several days later.

*Control of confounding factors* As many potential confounding factors as possible will be identified. Considering that this is an observational study, overly strict selection criteria are not used.

The design and implementation of this study are guided by statistical experts. Statistical methods such as standardized rate, stratified analysis, multivariate logistic regression analysis and propensity score matching will be adopted to identify the influential variables. These influential variables will be taken into consideration when calculating the annual rupture rate and when establishing the multifactor analysis model in CIAP-2.

Subgroup analyses and a case–control study design will be used when calculating the rupture rate in specific populations. The selection criteria for the exposure group and the control group will be set reasonably, and multiple groups of controls will be used if necessary.

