## Background

Cerebrovascular disease is one of the leading causes of death in China and contributes to a heavy disease burden [1]. The age-standardized prevalence, incidence, and mortality rates of stroke were 1114.8/100,000, 246.8/100,000 and 114.8/100,000 person-years, respectively, in China among those aged ≥ 20 years. Subarachnoid hemorrhage (SAH) accounts for 4.4% of cerebrovascular disease [2, 3]. Rupture of an intracranial aneurysm (IA) is the most common cause of SAH [4], which has very high morbidity and mortality [5]. A cross-sectional study of the community shows that the incidence of unruptured intracranial aneurysms (UIAs) is as high as 7% in the Chinese population of 35 to 75-year-old people [6]. Therefore, it is an urgent task to reduce the rupture risk and mortality rate.

It is critically important to clarify the natural history of UIAs and screen for risk factors for rupture. The International Study of Unruptured Intracranial Aneurysms (ISUIA) [7, 8] and Unruptured Cerebral Aneurysms Study (UCAS) [9] are the most influential studies of the natural course and annual rupture rate of UIAs. However, a relatively high degree of selectivity bias leads to lower external validity of their findings. There are still no reliable reports about the annual rupture rate of UIAs in Chinese populations.

Thus far, there is also a lack of a clear conclusion about the risk factors for rupture. Studies have shown that some factors might be related to the risk of aneurysm rupture, such as factors related to morphology (the largest diameter ≥ 7 mm, presence of ascus, etc.) [7] and pathological damage (endothelial instability, inflammatory cell infiltration, etc.). Racial factors also have a great deal of influence on the risk of aneurysm rupture. Scholars have established a “PHASES” UIA rupture prediction model based on the North American, Finnish, and Japanese populations through systematic reviews [10]. However, the results obtained by different research institutions are not consistent and might be impacted by research design and sample size. Thus, the applicability of the existing rupture model requires further verification [11].

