### Participating center qualification

The investigators will collaborate with the other 19 medical centers located in the different regions of China (Southeast, Southwest, Northwest and Northeast China). Each center has more than two referral units, has experience in the diagnosis of UIAs and has a skilled treatment team. Thus, it is believed that this cohort can adequately represent the population at the regional and national levels. During the study period, all the patients included in this study will be observed and treated in the collaborating medical centers.

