### Recruitment of participants

Patients will be enrolled consecutively in all of the clinical centers and through China’s Stroke Prevention Project Committee. Patients with UIAs will be enrolled when they first visit the clinical center or are registered by the Stroke Prevention Project Committee. Patients with multiple aneurysms will also be enrolled when at least one aneurysm remains untreated. The patients will be selected according to the following selection criteria.

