**Fig. 2 Fig2:**
[figure not shown]
Flow chart of CIA-1. *CRF* case report form

Taking advantage of the EDC system, it is possible to upload, browse and examine the data at the same time in different centers. The data can be centrally managed for consistent quality control. Every change in the patient’s information in the database will be recorded by the system, which will increase the reliability and credibility of the data.

Several measures have been taken to ensure that this nationwide large-scale multicenter project is implemented adequately according to the unique standards: (1) the EDC system has an instant error reporting function; (2) self-inspection is conducted in every clinical center on a monthly basis; (3) regular training is provided to the researchers; (4) a semiannual meeting is held to summarize the research and solve any problems in the study; (5) regular censoring is conducted by the CRO; and (6) the statistical experts will follow-up with this program and evaluate the credibility and effectiveness of the data.

In addition, this project establishes a Project Management Committee that is responsible for project design and implementation, summary and analysis of the data, and writing the research report. The following institutions are also established: (1) The Central Biological Specimen Bank and Central Laboratory is established to store, test and manage the specimens. Gene and biomarker detection are conducted in the central laboratory following unified standards. (2) The Medical Image Analysis Center is established to analyse, store and manage the DICOM data. A uniformed interpretation standard of medical imaging data is made by the MIAC. (3) The Information Managing Center is responsible for the construction and maintenance of the EDC system and ensuring the security, completeness and accuracy of the data.

Limitations also exist in this study. All of the participants are Chinese; thus, the conclusions can only represent the characteristics of the Chinese population. The credibility will be impaired if the conclusions are extrapolated to other races.

In addition, information asymmetry exists. For example, regular medical examinations are not widely implemented in some remote areas. In some remote areas, patients cannot arrive at the hospital in time when the aneurysm ruptures. The incidence rate of these occurrences remains unclear. For these populations, the rupture rate might be miscalculated in this study.

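### The study is labelled population-based and nationally representative, but the recruitment it describes does not support reading its overall rate as the rupture rate of all UIAs in China

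*Protocol article*

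**What the plan says.** Three parts of the protocol article bear on this.

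- **The claim.** Under Measures to reduce bias, as part of the control of selection bias: "This is a nationwide population-based study". Under Participating center qualification: "it is believed that this cohort can adequately represent the population at the regional and national levels".
- **The grounds for the claim.** The sentence just before the representativeness statement reads "Each center has more than two referral units, has experience in the diagnosis of UIAs and has a skilled treatment team". Measures to reduce bias adds "Twenty centers selected from different regions of China are involved in this study", and says that each centre screens consecutively.
- **The entry routes.** Recruitment of participants: "Patients with UIAs will be enrolled when they first visit the clinical center or are registered by the Stroke Prevention Project Committee".

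The end of the Background names the rupture rate in Chinese people as a main purpose, and the aims under Study design and methods repeat it. The Background also criticises the two large earlier cohorts: "However, a relatively high degree of selectivity bias leads to lower external validity of their findings". The limitations in the Discussion mention remote areas ("For example, regular medical examinations are not widely implemented in some remote areas") and over-treatment as possible sources of error in the rate.

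**The concern.** A population-based cohort starts from a defined population and either enumerates it or samples it. Here the starting point is a diagnosis that has already been made and has led to a clinic visit or a registration. Consecutive screening prevents picking and choosing among patients who reach a source. It says nothing about who reaches one. Spreading centres over regions widens geography but does not change the step from having an aneurysm to being diagnosed and referred.

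This matters because the Discussion itself reports rupture risk that varies steeply with size and location. A pooled rate is therefore partly a description of the enrolled case mix. If it is published as the national rate, it will be applied to aneurysms found in other ways, for which the mix may differ. Sampling error shrinks with enrolment; this source of error does not.

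**Working it through.** **1. Claim against design.** A population-based label needs a stated source population, a catchment area, or a probability sample of centres or patients. The article states none of these. It describes selected centres, two entry routes and consecutive screening. Referral links and treatment skill are reasons to expect good recruitment and good data, not reasons to expect representativeness.

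**2. The plan's precision.** Sample size calculation uses n = u²p(1−p)/d² with p = 1%, d = 0.6 percentage points and two-sided α = 0.05:

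1.96² × 0.01 × 0.99 / 0.006² = 1056.

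The stated 1173 a year is not this figure. It equals 1056.4 / 0.90 rounded down, which is a separate matter and does not affect the present point. At the stated four-year total of 4696, the 95% half-width is 1.96 × √(0.01 × 0.99 / 4696) = 0.28 points. That covers sampling error only.

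**3. How far case mix could move the rate.** Inputs from the documents: 0–2.5% over 5 years below 7 mm (Discussion), which divided by 5 is 0–0.5% a year, with midpoint 0.25%; and an expected overall rate of 1% (Sample size calculation). Inputs that are *assumed*: 80% of the enrolled aneurysms are small, 90% or 95% of those in the community are small, and size-specific rates are the same in both.

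With small-aneurysm rate s, the rate L for larger ones solves 0.8s + 0.2L = 1%. The community rate is then 0.9s + 0.1L or 0.95s + 0.05L.

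| s (% a year) | L (% a year) | Community rate, 90% small | Shift from 1% | Community rate, 95% small | Shift from 1% |
|---|---|---|---|---|---|
| 0 | 5 | 0.50 | 0.50 | 0.25 | 0.75 |
| 0.25 | 4 | 0.625 | 0.375 | 0.4375 | 0.5625 |
| 0.5 | 3 | 0.75 | 0.25 | 0.625 | 0.375 |

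The shift runs from 0.25 to 0.75 points. At the midpoint of the small-aneurysm range, both shifts are below the allowable error of 0.6. Only the corner with s = 0 and 95% small exceeds it. Five of the six shifts exceed the 0.28-point half-width.

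**4. The same question without assuming a direction.** Suppose, again as an assumption, that the kind of patient enrolled makes up half of all UIA patients and ruptures at 1%. If the other half ruptures at 0.5% or 1.5%, the national rate is 0.75% or 1.25%. The bias is 0.25 points in size, and the standard error at 4696 is 0.28/1.96 ≈ 0.145 points. The nominal 95% interval then covers the national rate about 59% of the time. If the enrolled kind makes up 80%, the bias is 0.1 points and coverage is about 89%.

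**The case against.** Much of the case on the other side stands.

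- **The limits are partly disclosed.** The Discussion says the rate may be wrong for remote populations and that over-treatment may distort it. The fault is an unqualified claim in two sections, not silence. The concession is partial because it does not extend to selection through diagnosis and referral in general.
- **The committee route is undescribed.** It may include community screening, and the committee is a national body that co-sponsors the project. A reader might infer that the study can say nothing about the national rate. The documents do not support that: they leave representativeness unestablished, not disproved.
- **Stratified work is planned.** Measures to reduce bias lists standardised rates and stratified analysis, and Statistical analysis plans subgroup rates. These lessen the risk of misapplying the pooled figure. However, no reference UIA population is named, and such methods cannot correct unmeasured selection.

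Other stronger readings also go too far. A reader might infer that people in remote areas are never examined; the text says only that regular examination is not widespread in some of them. A reader might take the 7% community figure in the Background to mean that almost all such people never attend these centres; nothing says so. A reader might say the study repeats the very flaw it finds in the earlier cohorts; the Background does not say which kind of selection it means.

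Nor is it established that the cohort's rate would be too high. Observation stops at surgery, so preferential treatment of larger aneurysms could push the rate the other way.

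**Conclusion.** The point holds as an over-claim. The label and the representativeness statement do not follow from the recruitment described, and the main aim inherits the gap. On the stated design, the pooled rate estimates rupture among diagnosed, initially untreated, eligible UIAs reaching these sources. Taking it as an unbiased rate for all UIAs in China needs an argument that the article does not give.

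The size and direction of any bias cannot be derived from the documents. The 0.25 to 0.75 points rest on assumed size mixes, on equal size-specific rates in both settings and on a 1% overall rate. They show that an error comparable with the plan's tolerance is possible, not that it will occur. The data remain useful; what must change is what may be concluded from them.

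**What to change.** 1. In Participating center qualification and Measures to reduce bias, describe the study as a multicentre hospital- and registry-based cohort, and remove or qualify the statement on national and regional representativeness.
2. At the end of the Background and in the aims under Study design and methods, restate the target as the yearly rupture rate of diagnosed, initially untreated UIAs from the 20 centres and the committee's registrations. Limit the conclusion to these.
3. Report the rupture rate separately by entry route and by size and location, next to the pooled rate.

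A figure re-weighted to the community survey should not be offered as the rate for the general UIA population. The documents do not give that survey's size and location distribution, its ages (35 to 75) differ from this cohort's, and re-weighting would bring back the claim that step 1 removes.

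The cost is rewording, knowing each participant's entry route, and a few more lines in the results tables. Recruitment, visits and sample size are untouched. The downside is a narrower headline claim and, with few ruptures expected, wide intervals in the smaller strata.

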### Statistical methods

#### Sample size calculation

The sample size is calculated based on the following formula:$$ n = \frac{{u_{\alpha }^{2} p\left( {1 - p} \right)}}{{d^{2} }} $$

The annual rupture rate is expected to be 1% [9], the allowable error is d = 0.6%, the tests will be two-sided, with an α level of 0.05. It is calculated that 1173 subjects need to be enrolled in 1 year, and 4696 subjects are needed in 4 years. The expected drop-out rate is 5%. Drop-out is identified as enrolled patients who cannot be included in the primary analysis because, for example, they did not complete the follow-up in time or they lack key information.

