## Discussion

An intracranial aneurysm is an abnormal bulging in the wall of the intracranial artery and is the most common cause of subarachnoid hemorrhage. Subarachnoid hemorrhage, mostly caused by the rupture of an UIA, is the third most common acute cerebrovascular disease, and the associated death and disability rate can be as high as 64%. It is an urgent task to control the risk factors and reduce the rupture rate of UIAs. It is equally important to reveal the natural history of UIAs and identify the risk factors for rupture.

It has been reported by UCAS that the natural course of unruptured cerebral aneurysms varies according to the size, location, and shape of the aneurysm. The annual rupture rate of UIAs is 0.95% (95% confidence interval 0.79–1.15). Larger aneurysms and those located in the posterior and anterior communicating arteries or that have a daughter sac are more likely to rupture [9]. The ISUIA also showed that the location and size of the aneurysm are predictors of rupture. Aneurysms located in the posterior circulation and posterior communicating artery rupture more easily than those located in the internal carotid artery, anterior communicating, anterior cerebral artery or middle cerebral artery. The 5-year cumulative rupture rates of aneurysms larger than 25 mm are as high as 40–50%. The 5-year cumulative rupture rates of aneurysms smaller than 7 mm are as low as 0–2.5% [7, 8].

Although some risk factors for rupture have been identified in these two large studies, the influence of other factors, such as drug history, disease history, genetics, lifestyle and stress from life and work, remain unclear. To date, the causes underlying the development of aneurysms are equally unclear. In addition, there are no reports about the rupture rate of UIAs in the Chinese population. The present study will describe the natural history of UIAs, calculate the annual rupture rate of the entire cohort as well as specific subgroups of patients, and identify the specific subgroups that have higher risks of rupture. The conclusions will provide evidence to guide the appropriate management of UIAs and develop a more reasonable UIA prevention and control strategy in China.

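### The stated non-response rule goes back only to the patient, so a fatal rupture that nobody reports may be treated as drop-out; by itself this lowers the rupture rate

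*Protocol article*

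**What the plan says.** The primary outcome is aneurysm rupture (Outcomes). The annual rate is a proportion taken from the 1-year assessment (Statistical analysis). The follow-up section makes the 3- and 12-month contacts by phone or Internet and the 6-month contact face to face. Table 1 lists end-point evaluation at 90, 180 and 365 days.

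Four statements bear on a rupture that kills before anyone reports it:

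- Measures to reduce bias, on non-response: "In the case of a nonresponding patient, the CRA will try to contact the patient again several days later". No further step is named. The same section promises a separate analysis of missing information but does not describe it.
- Sample size calculation: "Drop-out is identified as enrolled patients who cannot be included in the primary analysis". The examples given are follow-up not finished in time and absent key data. The expected share is 5%.
- Discussion, limitations: "In some remote areas, patients cannot arrive at the hospital in time when the aneurysm ruptures". The article adds that the frequency is unknown and that the rate could be wrong in these populations. It gives neither a direction nor a remedy.
- Discussion, on subarachnoid hemorrhage: "the associated death and disability rate can be as high as 64" per cent.

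**The concern.** A patient who has died of a rupture cannot answer a second call any more than the first. If no relative or hospital reports the death, the centre sees an unanswered contact and an empty 1-year assessment, and that fits the article's description of drop-out. The event then leaves the numerator, while the denominator loses one patient among thousands.

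The estimate at stake is the study's main one. Ruptures are few, so a handful of lost events shifts the rate, and a larger sample does not reduce the shift. A person-time or survival analysis does not restore an event that was never recorded. If such losses cluster in remote areas, as the limitations paragraph suggests they might, regional comparisons could be affected too; the documents give no figures for that.

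**Working it through.** **Inputs from the article (Sample size calculation).** "The annual rupture rate is expected to be 1" per cent; "the allowable error is d = 0.6" per cent; "the tests will be two-sided, with an α level of 0.05"; expected drop-out 5%. The stated result: "It is calculated that 1173 subjects need to be enrolled in 1 year, and 4696 subjects are needed in 4 years".

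**Input not in the documents.** f, the share of all ruptures that are fatal and unreported. It is assumed here to lie between 5% and 30%.

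**1. The plan's own figure.** n = z²p(1−p)/d² = 1.96² × 0.01 × 0.99 / 0.006² = 1056.4, so 1057. With 5% drop-out, 1056.4/0.95 = 1112.0, so 1113, and 4 × 1113 = 4452. With 10% drop-out, 1056.4/0.90 = 1173.8, so 1174, and 4 × 1174 = 4696. The printed figures therefore fit 10% drop-out rather than the stated 5%. That is a separate matter and nothing below depends on it. I use N = 4696 and 5% as stated.

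**2. Events against losses.** Expected ruptures: 4696 × 0.01 = 47.0. Expected drop-outs: 4696 × 0.05 = 234.8. The planned loss is about five times the number of events, so a low drop-out rate does not by itself protect the numerator.

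**3. Effect of the mechanism alone.** Suppose unreported fatal ruptures are dropped and all other drop-out is unrelated to rupture. With true rate p, the observed rate is p(1−f)/(1−pf).

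| Assumed f | Ruptures lost (47.0 × f) | Share of the 234.8 drop-outs | Rate reported when the true rate is 1.00% |
|---|---|---|---|
| 5% | 2.3 | 1% | 0.95% |
| 10% | 4.7 | 2% | 0.90% |
| 15% | 7.0 | 3% | 0.85% |
| 20% | 9.4 | 4% | 0.80% |
| 30% | 14.1 | 6% | 0.70% |

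For example, at f = 30%: 0.01 × 0.70 / (1 − 0.003) = 0.702%.

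**4. Comparison with random error.** The 95% half-width at N = 4696 is 1.96 × √(0.01 × 0.99/4696) = 0.28 points. The shift of 0.05 to 0.30 points runs from a small part of that to about its full size.

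**5. Why the net direction is open.** Suppose instead that every other drop-out is free of rupture. Removing those patients while keeping the known ruptures raises the rate. With all ruptures detected it would be 46.96/4461.2 = 1.05%. With f = 5% the two effects cancel: (46.96 − 2.35)/4461.2 = 1.00%. With f = 30% the result is (46.96 − 14.09)/4461.2 = 0.74%. The sign of the total drop-out bias therefore depends on facts that the documents do not give.

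**The case against.** The strongest reply is that this is a condensed article. Tracing steps, proxy contacts and review of deaths usually sit in the full protocol and the case report forms, which are not shown, and the list of baseline items is open-ended. This stands in part: a proxy contact may already exist. But the point does not rest on silence alone. The article chose to print its non-response step, its description of drop-out and its admission about remote areas, and these do not fit together.

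A reader might infer that every patient who dies of rupture before reaching hospital will be coded as a non-responder and removed. The documents do not say so. A relative may answer the call. The drop-out wording is a planning allowance with examples, not a rule for classifying deaths. A known rupture ends observation and moves the patient to another cohort of the project. Follow-up is also more than one unanswered call: there is a face-to-face contact at 6 months, end-point and adverse-event evaluation at three time points, and regular calls and messaging. All of this narrows the problem to ruptures that nobody reports. It does not remove it, because each of these routes needs the patient or someone else to come forward.

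A reader might also take the 64% as the share of ruptures that could be lost. That figure combines death with disability and says nothing about unreported deaths before hospital; disabled survivors may be in hospital or reachable through family. Finally, a reader might conclude that the reported rate must be too low overall. Step 5 of the working shows that this does not follow.

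The limitations paragraph does disclose part of the problem, and the promised analysis of missing information may be detailed elsewhere. Neither changes how events are found.

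**Conclusion.** The concern holds in limited form. Under the published rules, a fatal rupture that nobody reports may end up among the drop-outs, and this mechanism can only lower the rupture rate. With 5% to 30% of ruptures assumed fatal and unreported, a true 1.00% would be reported as about 0.95% to 0.70%. That range is an assumption, as is the premise that other drop-out is unrelated to rupture. The documents support the direction of this one mechanism, but not its size and not the net bias from all drop-out. The change should be made, with medium confidence, because the main outcome is affected, the events are few and the remedy is cheap.

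**What to change.** First check whether the full protocol or the enrolment form already provides for a proxy contact and a rule for deaths; if so, state it. Otherwise:

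1. Record a proxy contact in CRF-A at enrolment. For patients already enrolled, collect it at the next contact.
2. Amend the non-response rule in Measures to reduce bias. After a failed repeat contact, the existing research associate calls the proxy, and the local hospital if known, to establish vital status and the date and circumstances of any death.
3. Do not class a patient known to have died as a drop-out. State how deaths from other causes within the year enter the proportion.
4. In the primary analysis, count as ruptures those deaths with subarachnoid hemorrhage confirmed or reported by a physician.
5. Add a sensitivity analysis that also counts sudden unexplained deaths as ruptures. Do not call it an upper bound, because untraced patients remain outside it.
6. Report the number of patients with unknown vital status and give a separate scenario for them. Counting all 234.8 planned drop-outs as ruptures would give (4461.2 × 0.01 + 234.8)/4696 = 5.95%, too extreme to be useful, so tracing matters more than modelling.

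The cost is one form field, one or two extra analyses, and additional calls for about 5% of patients (234.8/20, or about 12 per centre over the study). The downside is that proxy reports are less certain than hospital records. The sensitivity analyses show how much this matters but do not remove it.
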